## Abstract

**Background:**

Feedback is potentially effective in improving the quality of care. However, merely sending reports is no guarantee that performance data are used as input for systematic quality improvement (QI). Therefore, we developed a multifaceted intervention tailored to prospectively analyzed barriers to using indicators: the Information Feedback on Quality Indicators (InFoQI) program. This program aims to promote the use of performance indicator data as input for local systematic QI. We will conduct a study to assess the impact of the InFoQI program on patient outcome and organizational process measures of care, and to gain insight into barriers and success factors that affected the program's impact. The study will be executed in the context of intensive care. This paper presents the study's protocol.

**Methods/design:**

We will conduct a cluster randomized controlled trial with intensive care units (ICUs) in the Netherlands. We will include ICUs that submit indicator data to the Dutch National Intensive Care Evaluation (NICE) quality registry and that agree to allocate at least one intensivist and one ICU nurse for implementation of the intervention. Eligible ICUs (clusters) will be randomized to receive basic NICE registry feedback (control arm) or to participate in the InFoQI program (intervention arm). The InFoQI program consists of comprehensive feedback, establishing a local, multidisciplinary QI team, and educational outreach visits. The primary outcome measures will be length of ICU stay and the proportion of shifts with a bed occupancy rate above 80%. We will also conduct a process evaluation involving ICUs in the intervention arm to investigate their actual exposure to and experiences with the InFoQI program.

**Discussion:**

The results of this study will inform those involved in providing ICU care on the feasibility of a tailored multifaceted performance feedback intervention and its ability to accelerate systematic and local quality improvement. Although our study will be conducted within the domain of intensive care, we believe our conclusions will be generalizable to other settings that have a quality registry including an indicator set available.

**Trial registration:**

Current Controlled Trials ISRCTN50542146

## Background

To systematically monitor the quality of care and develop and evaluate successful improvement interventions, data on clinical performance are essential [1,2]. These performance data are often based on a set of quality indicators, ideally combining measures of structure, process, and outcomes of care [3,4].

Also within the domain of intensive care, several indicator sets have been developed [5-9], and numerous quality registries have been established worldwide to routinely have indicator data available on the performance of intensive care units (ICUs) [10-13]. In the Netherlands, the National Intensive Care Evaluation (NICE) quality registry was founded in 1996 by the Dutch intensive care profession with the aim to systematically and continuously monitor, assess, and compare ICU performance, and to improve the quality of ICU care based on the outcome indicators case-mix adjusted hospital mortality and length of ICU stay [13]. In 2006, this limited core data set of outcome indicators was extended to a total of eleven structure, process, and outcome indicators, adding items such as nurse-to-patient ratio, glucose regulation, duration of mechanical ventilation, and incidence of severe pressure ulcers. The extended set was developed by the Netherlands Society for Intensive Care (NVIC) in close collaboration with the NICE foundation [7].

Besides facilitating data collection and analyses, NICE-like most quality registries-also sends participants periodical feedback reports on their performance over time and in comparison with other groups of ICUs. Although feedback is potentially effective in improving the quality of care [14-16], merely sending feedback reports is no guarantee that performance data are used as input for systematic quality improvement (QI).

### Problem: barriers perceived by health care professionals to using performance feedback for systematic quality improvement

Previous systematic reviews reported potential barriers at different levels to using performance data for systematic improvement of health care, *e.g.*, insufficient data quality, no acknowledgement of the room for improvement in current practice, or lack of resources to implement quality interventions [15,16]. The results of a validated questionnaire completed by 142 health care professionals working at 54 Dutch ICUs confirmed that such barriers also exist within the context of intensive care [17]. As suggested by others [18,19], we translated these prospectively identified barriers into a multifaceted QI intervention using input from future users, expert knowledge, and evidence from literature. The table in 'Additional file 1' contains all barriers identified and how they are targeted by the intervention. We named the resulting QI program InFoQI (Information Feedback on Quality Indicators). InFoQI was developed and will be evaluated within the context of intensive care and the Dutch NICE registry. By targeting the potential barriers to using performance feedback as input for systematic QI activities at ICUs, the InFoQI program ultimately aims to improve the quality of intensive care.

### Study objectives

The study as proposed in this protocol aims to evaluate the effect of the tailored multifaceted feedback intervention on the use of performance indicator data for systematic QI at ICUs. Specific objectives include:

1. To assess the impact of the InFoQI program on patient outcome and organizational process measures of ICU care.

2. To gain insight into the barriers and success factors that affected the program's impact.

3. The InFoQI program was designed to overcome the previously identified barriers to using performance indicator data as input for local QI activities. Based on this assumption we hypothesize that ICUs participating in the InFoQI program will improve the quality of their care significantly more than ICUs receiving basic feedback from the NICE registry.

The results of this study will inform those involved in providing ICU care on the feasibility of the InFoQI program and its ability to accelerate systematic, local QI at ICUs. More in general, we believe that our results might be of interest to clinicians and organizations in any setting that use a quality registry including performance indicators to continuously monitor and improve the quality of care.

## Methods

### Study design

We will execute a cluster randomized controlled trial to compare facilities participating in the InFoQI program (intervention arm) to facilities receiving basic feedback from the NICE registry (control arm). Because the InFoQI program will be implemented at the facility rather than individual level, a cluster randomized trial is the preferred design for the evaluation of the program's effectiveness [20]. Like most trials aimed at evaluating organizational interventions, our study is pragmatic [21]. To apply to current standards, the study has been designed and will be reported in accordance with the CONSORT statement [22] and the appropriate extensions [23,24].

### Setting

The setting of our study is Dutch intensive care. In the Netherlands, virtually all 94 ICUs are mixed medical-surgical closed-format units, *i.e.*, units with the intensivist as the patient's primary attending physician. The units are a mixture of academic, teaching, and nonteaching settings in urban and nonurban hospitals. In 2005, 8.4 adult ICU beds per 100,000 population were available, and 466 patients per 100,000 population were admitted to the ICU that year [25]. Currently, a representative sample of 80 ICUs-covering 85% of all Dutch ICUs-voluntarily submit the limited core data set to the NICE registry, and 46 of them collect the complete, extended quality indicator data set.

At the NICE coordination center, dedicated data managers, software engineers, and a coordinator are responsible for routine processing, storing, checking, and reporting of the data. Also, for the duration of the study, two researchers will be available to provide the InFoQI program to ICUs in the intervention arm. The availability of these resources is essential for the feasibility of our study.

### Selection of participants

All 46 ICUs that participate in NICE and (are preparing to) submit data to the registry on the extended quality indicator set will be invited to participate in our study. They should be willing and able to allocate at least two staff members for an average of four hours per month to be involved in the study. The medical manager of the ICU must sign a consent form to formalize the organization's commitment.

All patients admitted to participating ICUs during the study period will be included in the analyses. However, when evaluating the impact on patient outcomes, we will exclude admissions based on the Acute Physiology and Chronic Health Evaluation (APACHE) IV exclusion criteria [26], as well as admissions following cardiac surgery, patients who were dead on admission, and admissions with any of the case mix variables missing.

### Control arm: basic feedback from the NICE registry

The ICUs allocated to the control arm will be treated as 'regular' NICE participants. This implies they will receive basic quarterly and annual feedback reports on the registry's core outcome indicators case-mix adjusted hospital mortality and length of ICU stay. In addition, they will be sent similar, but separate, basic quarterly and annual feedback reports containing data on the extended indicator set. Also, support by the NICE data managers is available and includes data quality audits, support with data collection, and additional data analyses on request. Furthermore, they are invited to a yearly discussion meeting where they can share experiences with other NICE participants.

### Intervention arm: the InFoQI program

ICUs assigned to the intervention arm, *i.e.*, participating in the InFoQI program, will receive the same intervention as the control arm, but extended with more frequent and more comprehensive feedback, a local, multidisciplinary QI team, and two educational outreach visits (Table 1).

**Table 1 T1:** Elements of the InFoQI program (intervention arm)

Element	Description
Feedback	• monthly report for monitoring ICU's performance over time
reports	• comprehensive quarterly report for benchmarking ICU's performance to other
	groups of ICUs
	• sent to and discussed by QI team members
Local QI team	• multidisciplinary • responsible for formulating and executing a QI action plan • monthly monitoring and discussing of performance using feedback reports • sharing main findings with rest of ICU staff
Educational outreach visits	• on-site (1) at start of study period and (2) after six months • all QI team members are present; visits guided by principal investigators • promoting use of Plan-Do-Study-Act cycle for systematic quality improvement • formulating and evaluating QI action plan based on performance data

From the prospective barriers analysis, it appeared that many barriers concerned the basic NICE feedback reports. To target the lack of case-mix correction and lack of information to initiate QI actions, the basic quarterly report will be replaced by an extended, comprehensive quarterly report that facilitates comparison of an ICU's performance with that of other ICUs, *e.g.*, by providing the median length of ICU stay for elective surgery admissions in similar-sized ICUs as a benchmark. To increase the timeliness and intensity of reporting, we also developed a monthly report focusing on monitoring an ICUs' own performance over time to facilitate local evaluation of QI initiatives, *e.g.*, by providing Statistical Process Control (SPC) charts [27]. To decrease the level of data aggregation, both the monthly and quarterly reports contain data at the level of individual patients, *e.g.*, a list of unexpected non-survivors (*i.e.*, patients who died despite their low risk of mortality). The table in 'Additional file 2' summarizes the content of the reports.

ICUs in the intervention arm will establish a local QI team, creating a formal infrastructure at their department for systematic QI. This team must consist of at least one intensivist and one nurse; a management representative and a data manager are suggested as additional members. To target the lack of motivation to change, team members should be selected based on their affinity and experience with measuring and improving quality of care and their capability to convince their colleagues to be involved in QI activities. The team's main tasks are described in a protocol and include formulating a QI action plan, monitoring of performance using the feedback reports, and initiating and evaluating QI activities (see Table 1). We estimate the minimum time investment per team member to be four hours on average per month. This estimation takes into account all activities prescribed by the InFoQI program except for the execution of the QI plan. The actual time spent will depend on the type and number of QI actions in the plan.

Each ICU will receive two on-site educational outreach visits that are aimed at increasing trust in data quality, supporting the QI team members with interpreting their performance data, identifying opportunities for improvement, and translating them into a QI action plan. The structure of the visits will be equal for all intervention ICUs and the template for the action plan will be standardized. All visits will be facilitated by the same investigators who have a non-medical background; they have been involved in the development of the extended NVIC indicator set and have several years of experience with optimization of organizational processes at the ICU. Having non-clinicians supporting the QI team will make the intervention less intrusive, and therefore less threatening to participating units. It also increases the feasibility of the study, because clinical human resources are scarce in intensive care.

### Outcome measures

We used previously collected NICE data (regarding the year 2008) to select outcome measures from the extended quality indicator set to evaluate the effectiveness of our intervention. To decrease the probability of finding positive results by chance as a result of multiple hypothesis testing [28], we limited our primary endpoints to a combination of one patient outcome and one organizational process measure. We selected the indicators that showed the largest room for improvement, *i.e.*, the largest difference between the average of top-performing centers and the average of the remaining centers [29].

Primary outcome measures will be:

1. Length of ICU stay (ICU LOS); this will be calculated as the difference in days between the time of ICU discharge and time of ICU admission. To account for patients being discharged too early, the length of stay of the first ICU admission will be prolonged with the length of stay of subsequent ICU readmissions within the same hospital admission.

2. Proportion of shifts with a bed occupancy rate above 80%; this threshold is set by the NVIC in their national organizational guideline for ICUs [30]. We will calculate the bed occupancy rate as the maximum number of patients admitted simultaneously during an eight-hour nursing shift divided by the number of operational beds in that same shift. A bed will be defined as 'operational' when it is fitted with monitoring and ventilation equipment and scheduled nursing staff.

Secondary outcome measures will be all-cause, in-hospital mortality of ICU patients, duration of mechanical ventilation, proportion of glucose measurements outside the range of 2.2 to 8.0 mmol/L, and the proportion of shifts with a nurse-to-patient ratio below 0.5.

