### Data collection

We will use the existing data collection methods as currently applied by the NICE registry [31]. Most ICUs participating in NICE combine manual entry of data using dedicated software with automated data extractions from electronic patient records available in, *e.g.*, their patient data management system. Each month, participants upload their data from the local, electronic database to the central, electronic registry database. ICUs in the intervention arm that have not submitted their data at the end of a month will be reminded by phone, and assisted if necessary. Quarterly reports are provided within ten weeks after the end of a period, and monthly reports within six weeks. The NICE registry uses a framework for data quality assurance [32], including elements like periodical on-site data quality audits and automated data range and consistency checks. For each ICU, additional data checks for completeness and accuracy will be performed before, during, and after the study period using descriptive statistics.

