### Randomization

We will randomly allocate ICUs (clusters) to one of both study arms, stratified by the number of ventilated, non-cardiac surgery admissions (less than the national median versus more than the national median), and involvement in a previous pilot study to evaluate feasibility of data collection of the NVIC indicator set [7] (involved versus not involved). Each stratum will consist of blocks with a randomly assigned size of either two or four ICUs (see Figure 1). A researcher-not involved in the study and blinded to the identity of the units-will use dedicated software to generate a randomization scheme with an equal number of interventions and controls for each block. The size and the randomization scheme of the blocks will be concealed to the investigators enrolling and assigning the ICUs. In an email to the ICU confirming the arm to which they have been allocated, the researcher that executed the randomization process will be sent this information in copy as an additional check on the assignment process. Due to the character of the intervention, it will not be possible to blind participants or the investigators providing the InFoQI program.

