### Statistical analysis

For ICUs in the intervention group, the time from randomization to the first outreach visit-with an expected duration of six to eight weeks-will be regarded as a baseline period. Follow-up will end three months after the last report has been sent, assuming this is the average time required for an ICU to read, discuss, and act on a feedback report. The expected duration for intervention ICUs will therefore be approximately fourteen months. Control ICUs will have a fixed baseline period of two months, and a follow-up of fourteen months.

To assess the effect of the InFoQI program, the outcome values measured during the follow-up period will be compared between both study arms. To assess the effect of the program on length of stay, we will perform a survival analysis of time to alive ICU discharge with dying at the ICU as a competing risk [33], and adjusting for patient demographics, severity of illness during first 24 hours of admission, and admission type. To account for potential correlation of outcomes within ICUs, we will use generalized estimation equations with exchangeable correlation [34-36]. The same procedure will be used to analyze duration of mechanical ventilation. For all-cause mortality, logistic regression analysis will be used, adjusting for severity of illness at ICU admission by using the APACHE IV risk prediction model [26].

To assess the effect of the intervention on the proportion of shifts with a bed occupancy rate above 80%, shift-level occupancy data (0 for an occupancy rate below or equal to 80%, 1 for a rate above 80%) will be analyzed with logistic regression analysis. In this case, generalized estimation equations with an autoregressive correlation structure will be used to account for the longitudinal nature of shift occupancy observations. The same procedure will be followed to analyze the proportion of shifts with a nurse-to-patient ratio below 0.5.

To assess the effect on the proportion of out-of-range glucose measurements, multi-level logistic regression analysis will be performed where subsequent glucose measurements on the same patient are treated as time series data, and both patient-level and ICU-level intercept estimates are used to account for potential correlation of measurements within patients and within ICUs.

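### The glucose outcome is counted per measurement, so a change in rechecking after out-of-range values in one arm could move it with no change in glycaemia; add a per-shift analysis

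*Protocol article*

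**What the plan says.** The protocol article, under Outcome measures, lists as a secondary outcome the "proportion of glucose measurements outside the range of 2.2 to 8.0 mmol/L". The denominator is the individual measurement; no per-patient, per-day or time-weighted form is given.

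Under Statistical analysis, the model is a multi-level logistic regression that handles repeated values in a patient as a time series. The purpose given for its clustering terms is correlation alone: "both patient-level and ICU-level intercept estimates are used to account for potential correlation of measurements within patients and within ICUs". Follow-up values are compared between arms.

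The data are routine. The Data collection section says "We will use the existing data collection methods as currently applied by the NICE registry", and no common glucose sampling schedule is stated anywhere.

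Glucose belongs to the indicator set on which the program works: the Background describes the 2006 extension as "adding items such as nurse-to-patient ratio, glucose regulation". Table 1 gives the intervention teams the task of "monthly monitoring and discussing of performance using feedback reports", along with writing and carrying out an action plan. The trial is open; under Randomization, "it will not be possible to blind participants or the investigators providing the InFoQI program".

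**The concern.** A proportion of measurements equals the proportion of time out of range only if the chance of being sampled does not depend on the glucose value. If a unit rechecks sooner after an out-of-range value, out-of-range time is over-represented, and the degree depends on the recheck interval.

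The program exists to change unit practice, and rechecking is one practice that a team working on glucose might change. If that happens in one arm only, the comparison mixes a change in glycaemia with a change in measuring. Faster rechecking would make the indicator look worse and slower rechecking would make it look better, with glucose the same in both cases. The planned intercepts describe how alike the values are within a patient or an ICU. They do not describe why a value was taken when it was.

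**Working it through.** The protocol gives no glucose rate, sampling interval, effect size or power for this outcome, so there is no figure to reproduce. Everything below is an illustration. From the protocol come the 2.2 to 8.0 mmol/L range, the measurement as unit, the type of model, the eight-hour shift, and 26 ICUs (taken as 13 per arm). All glucose and interval parameters are assumed.

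**Step 1: closed form for the crude share.** Let p be the true share of time out of range, and let Tin and Tout be the hours to the next measurement after an in-range and an out-of-range value. If glucose changes slowly,

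measured share = (p/Tout) / [p/Tout + (1 − p)/Tin].

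With Tin = 4 h:

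| p | Tout = 4 h | Tout = 2 h | Tout = 1 h |
|---|---|---|---|
| 0.20 | 0.20 | 0.33 | 0.50 |
| 0.30 | 0.30 | 0.46 | 0.63 |
| 0.40 | 0.40 | 0.57 | 0.73 |

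For example, p = 0.30 and Tout = 2 give 0.15/(0.15 + 0.175) = 0.46. The crude odds ratio against Tout = 4 is Tin/Tout: 2.0 for 2 h and 4.0 for 1 h. These are crude figures under slow change, not output of the planned model.

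**Step 2: the type of model that is planned.** The same hourly autocorrelated glucose process was simulated in both arms, with 13 ICUs per arm, 100 patients per ICU and 6 replicates. Control ICUs sample every 4 h; only the sampling rule in the other arm varies. The fit was a patient random-intercept logistic model, then the same with the previous value added as one reading of the time-series treatment. The ICU intercept was left out of the fit.

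| Other arm: h after in-range / out-of-range value | Measured share, control v other | OR, patient intercept (SE of log OR) | OR, previous value added (SE of log OR) |
|---|---|---|---|
| 4 / 4 | 0.29 v 0.30 | 1.06 (0.04) | 1.03 (0.03) |
| 4 / 2 | 0.30 v 0.40 | 1.40 (0.09) | 1.27 (0.04) |
| 4 / 1 | 0.31 v 0.55 | 2.17 (0.09) | 1.72 (0.05) |
| 2 / 2 | 0.30 v 0.31 | 1.07 (0.07) | 1.02 (0.04) |

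The true share was about 0.29 to 0.31 in every arm. The model shrinks the artefact but does not remove it. Denser sampling whatever the value (last row) cannot be told from the same rule in both arms (first row).

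**Step 3: candidate corrections.** One autocorrelated process, true share about 0.31, sampled every 4 h in range, gave these shares. Crude odds ratios against the 4 h column are in brackets, for example (0.42/0.58)/(0.31/0.69) = 1.61.

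| Summary | Recheck 4 h | 2 h | 1 h |
|---|---|---|---|
| All measurements | 0.31 | 0.42 (1.61) | 0.55 (2.72) |
| First value per eight-hour shift | 0.31 | 0.32 (1.05) | 0.33 (1.10) |
| Each value carried forward to the next | 0.31 | 0.27 (0.82) | 0.24 (0.70) |

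A separate run with a true share of about 0.30 agreed: all measurements 0.30, 0.42 and 0.56; first per shift 0.32 and 0.33 for 2 h and 1 h rechecks; carried forward 0.27 and 0.25. Carrying forward errs the other way because a return to range is seen quickly, while the start of an excursion goes unseen until the next 4 h sample.

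**The case against.** The strongest objection is that the premise is not documented. Nothing in the protocol says that sampling depends on the last value, and nothing in the program prescribes a change in rechecking. Glucose regulation is one of eleven indicators, the section on related studies says that the program does not push one specific practice, and control ICUs also receive reports on the extended set. Practice differences that exist before randomization are balanced in expectation, so bias needs a change in one arm. All of this stands. It makes the point conditional; it does not make it wrong, because the intervention is meant to change practice in one arm.

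Three stronger readings are tempting and should not be drawn:
- A reader might infer that any difference in sampling frequency between units biases the outcome. It does not: uniformly denser sampling gave no shift beyond simulation noise.
- A reader might take the crude odds ratio of 2.0 as the expected bias. It is neither an estimate for this trial nor what a patient-intercept model returns for the same change (1.40, or 1.27 with the previous value).
- A reader might say that every measurement counts equally in the arm comparison. That describes the outcome definition. With patient and ICU intercepts, a heavily sampled patient does not contribute simply in proportion to the number of readings.

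It can also be said that the registry indicator was chosen deliberately and that sensitivity analyses belong in an analysis plan that is not shown. The first is a good reason to keep the indicator as the stated outcome. On the second, the protocol itself fixes both the unit and the model, and the weakness lies in that pairing; the remedy can sit in the analysis plan.

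**Conclusion.** The point holds as a conditional weakness in one secondary outcome. If rechecking after out-of-range values changes in one arm only, the planned analysis can report a glucose difference where there is none, and it has no means of telling the two apart. In the illustration the spurious odds ratio was about 1.3 to 1.4 for a change from 4 h to 2 h rechecks and about 1.7 to 2.2 for 4 h to 1 h. Those figures rest on an assumed glucose process, assumed intervals and a fit without the ICU intercept. The size, and even the presence, of such a bias in this trial cannot be derived from the protocol. Neither primary outcome nor the sample size is touched.

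**What to change.** Keep the registry indicator as the stated outcome, so that it matches what the ICUs are shown in their reports. Then pre-specify:
1. An analysis of the first glucose value per patient per eight-hour shift in the same multi-level logistic model. The shift is already a unit in this protocol, for bed occupancy.
2. A comparison between arms of glucose measurements per patient-day, overall and after out-of-range values.
3. A reading rule: a difference in the registry indicator is interpreted as a change in glycaemia only if the per-shift analysis agrees.

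Do not use carry-forward time weighting as the main correction, since it biases in the opposite direction.

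The cost is a few lines of analysis-plan text and modest programming, with no new data collection provided that measurement times are held. The planned time-series treatment suggests that they are, but the protocol does not say so and this should be confirmed. The per-shift analysis also uses fewer values, so it will be somewhat less precise.
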